### Credibility assessment

The Credibility of Treatment Rating Scale will be used to assess the credibility of the acupuncture treatments. This four-item scale is specially designed to assess the credibility of acupuncture [43]. It assesses participants’ “confidence in the treatment to alleviate their complaint,” “confidence in recommending the treatment to their friends who have similar complaints,” “perceived logic of the treatment,” and “likelihood that the treatment would alleviate their other complaints.”

### Blinding success assessment

After the final treatment, the success of blinding will be tested by asking participants in the acupuncture treatment group and the sham acupuncture group the following question: “When you volunteered for the trial, you were informed that you had an equal chance of receiving traditional acupuncture or acupuncture-like simulation treatment. Which acupuncture do you think you received?” Three response options will be provided for patients to choose from: acupuncture treatment, acupuncture-like simulation treatment, and uncertain. Those who choose either acupuncture treatment or acupuncture-like sham will be asked to provide a reason why they have made that assumption [9].

### Monitoring

#### Data and safety monitoring plan

A Data and Safety Monitoring Board (DSMB) will be formed according to the National Institutes of Health (NIH) to monitor the study progress and review safety and quality of data [44]. The committee consists of three members, including a senior acupuncturist, a pain specialist, and a biostatistician. The DSMB is independent of the proposed study and all the committee members will have to declare any conflict of interest in the study. Regular board meetings will be held to ensure that data are collected scientifically and ethically and subjects are not exposed to unnecessary risks [44].

### Data processing and analysis

#### Data management

Data will be collected by blinded assessors. All data will be double-entered and checked for consistency prior to analyses. If an immediate entry is not possible, data collected in paper form will be scanned and coded with subjects’ codes. All the data collected will be locked, and the Personal Data (Privacy) Ordinance (CAP 486) in Hong Kong will be complied with.

#### Statistical analyses

Statistical analyses will be performed using Statistical Product and Service Solutions (SPSS) 22 (or above) for Windows (SPSS, Chicago, IL, USA) or SAS. The intention-to-treat (ITT) approach will be used. Descriptive analyses will be done on baseline demographics.

To analyze the primary outcome, AUC of the NRS pain scores at rest will be calculated by plotting on the timescale using the trapezoidal method, and the comparisons between groups will be made using the Student’s *t* test. Missing NRS scores will be replaced by linear interpolation in cases if the missing scores fall between two valid scores, or by multiple imputations if the missing score is the last pain score taken on day 5.

The NRS pain scores while coughing will be analyzed in the same way as the pain scores at rest. For other secondary outcomes, cumulative morphine assumption between the two groups will be compared with Student’s *t* test or the Wilcoxon rank-sum test; time-to-event data will be analyzed by the method of survival analysis. Median time to event will be calculated using the Kaplan-Meier product limit estimator, and log-rank test will be used to determine the statistical significance of the treatment difference in the survival curves for those time-to-event variables. Analyses of secondary outcomes are not part of the power calculations of the study, and should, therefore, be considered exploratory. All tests are two-tailed, and a *p* value of less than 0.05 is considered statistically significant. The effect size will be estimated by Cohen’s *d* which is the mean difference between groups per pooled standard deviation. The mean difference and its 95% confidence interval will also be calculated using SPSS.

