### Participants

#### Sample size estimation

Results from an earlier study of EA as an adjunct treatment in postoperative pain were used for sample size consideration [10], and the expected mean difference and standard deviations of AUC in 5 days for the treatment group and control group were obtained by simulation using R [21].

The mean difference of AUC between treatment group and sham group in the previous study [10] is 3.4 with standard deviations of 2.9 for the treatment group and 3.6 for the sham group (effect size = 1.04). A lower limit of the 70% confidence interval of the effect size which is 0.75 is applied [22]. A sample size of 30 per group can provide 80% power to reject the null hypothesis with a significance level of 0.05 using a two-sided, two-sample, unequal-variance *t* test. With an expected dropout rate of 15%, the final sample size is 72 (36 per group). AUC is used to calculate the primary outcome measure because it provides information regarding the pain relief across the whole period, which is more meaningful than comparing the pain score at a particular time point. AUC also has an advantage in that it avoids multiple comparisons and thus will not inflate type I error. This statistical analysis approach has been widely used and reported by previous studies, including those published in leading pain journals [23, 24].

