### Randomization

Block randomization with a random block size ranging from 4 to 8 will be used in this study. Participants are randomly assigned to one of the two groups in 1:1 ratio after completion of baseline assessment, according to a randomized block list generated by an independent research assistant using R and the code will be kept in opaque sequentially numbered envelopes.

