## Discussion

The study protocol of the proposed trial will be conducted at the Queen Merry Hospital which is under the Hong Kong HA. Unlike many hospitals in the West and in China, acupuncture has become a routine in-patient service [45–47]. However, currently, acupuncture is not available in the Hong Kong HA system. The present study is designed to investigate whether it is feasible, effective and safe to use acupuncture as an adjunctive therapy for patients who suffer from postoperative pain and discomfort. If successful, the study would provide useful information for integrating acupuncture into perioperative care as part of the effort of integrating Chinese and Western medicine in Hong Kong hospitals.

This study protocol faces several challenges and limitations. Firstly, patients with different types of gynecological neoplasia requiring laparotomy will be included, which may create variability in the population. However, as wound pain is the main target of treatment, the variation of types of neoplasm would not be a great problem. To address this issue, only patients with midline incision are recruited, which would likely involve similar degrees of wound pain being experienced by each patient. In addition, randomization will be done rigorously so that the types of neoplasm in the two groups can be balanced.

Secondly, although in many of the previous trials on postoperative abdominal surgical pain, acupuncture was performed before the induction of anesthesia in the operating theater [3, 13, 31], it is infeasible to conduct preoperative acupuncture in our operating theaters which will lengthen the interval time between preoperative acupuncture being performed and the actual operation. This is because the surgical team was concerned about the underlying risks and potential liability. Therefore, in this trial, preoperative treatment will be carried out in the ward within 2 h before the operation.

Thirdly, the surgery time is uncertain and often varies due to the nature of the various underlying diseases, making it difficult to schedule an acupuncture treatment. To solve this problem, preoperative acupuncture will be arranged based on the estimated time of the operation list and the first postoperative treatment will be done upon arrival on the ward. The exact operation time and acupuncture treatment time will be recorded for further analysis.

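### The primary test (Student's t) is not the unequal-variance test used for the sample size, and unstratified blocks balance neoplasm type only in expectation; the cost is small and concerns precision and credibility, not validity

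*Protocol article*

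**What the plan says.** All references are to the protocol article.

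- **Sample size estimation.** An earlier study supplies a mean AUC difference of 3.4 with SDs of 2.9 (treatment) and 3.6 (sham), an effect size of 1.04. The design value is reduced to 0.75. The power statement is "A sample size of 30 per group can provide 80% power to reject the null hypothesis with a significance level of 0.05", obtained "using a two-sided, two-sample, unequal-variance *t* test". Allowing for 15% dropout, the total is 72.
- **Statistical analyses.** The AUC of NRS at rest will be calculated "and the comparisons between groups will be made using the" Student's t test. No covariate is named. Cohen's d is defined with the pooled SD.
- **Randomization.** "Block randomization with a random block size ranging from 4 to 8 will be used in this study", in a 1:1 ratio. No stratification factor is named.
- **Discussion, first limitation.** Mixed neoplasm types may create variability. The reply is that wound pain is the treatment target and that only midline incisions are recruited. It then adds that "randomization will be done rigorously so that the types of neoplasm in the two groups can be balanced".

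**The concern.** Two statements about the primary comparison do not fit together, and one stated safeguard is not delivered by the design.

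First, the trial is powered on one t test and analysed with another. The planning SDs differ by arm, which is presumably why the unequal-variance test was used for the sample size. The pooled test keeps its level under unequal variances when the arms are the same size, but not when they differ. As written, an analyst could cite either section and report either p value.

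Second, permuted blocks keep the arm sizes close over time. They do nothing for neoplasm type, however carefully the list is generated and concealed. With 36 per arm the mix of ovarian, uterine and cervical disease is left to chance, and the named primary analysis does not adjust for it. What is at stake is some precision, and the credibility of the comparison if a visible imbalance occurs.

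**Working it through.** **1. The plan's own figures reproduce.**

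- Pooled SD = √[(2.9² + 3.6²)/2] = √10.685 = 3.269, and 3.4/3.269 = 1.04, as stated.
- Design difference = 0.75 × 3.269 = 2.452.
- At 30 per group, SE = √[(8.41 + 12.96)/30] = 0.844, so the noncentrality is 2.452/0.844 = 2.905.
- Student df = 58. Welch (Satterthwaite) df = 29 × (8.41 + 12.96)²/(8.41² + 12.96²) = 55.5.
- Power from the noncentral t: 81.5% (Student), 81.4% (Welch). At 29 per group both give 80.1%, so 30 is adequate under either test.
- 30/0.85 = 35.3, rounded up to 36 per group, 72 in total. At 36 per group, power is 88.1% (Student) and 88.0% (Welch).

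**2. Effect of the test mismatch.** With equal n the two t statistics are identical and only the df differ. With unequal n they separate, because the pooled variance is weighted towards the larger arm. Taking 36 acupuncture (SD 2.9) and 26 sham (SD 3.6):

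- True variance of the difference = 8.41/36 + 12.96/26 = 0.732, SE 0.856.
- Pooled variance = (35 × 8.41 + 25 × 12.96)/60 = 10.306; times (1/36 + 1/26) = 0.683, SE 0.826.
- Student's SE is therefore about 3.4% too small (0.826/0.856 = 0.966). With 26/36 the same arithmetic gives √0.733/√0.683 = 1.036, about 3.6% too large.

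Simulated two-sided type I error at nominal 0.05, with these SDs:

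| Completers, acupuncture/sham | Student | Welch |
|---|---|---|
| 30/30 and 36/36 | 0.050 | 0.050 |
| 33/27 | 0.055 | 0.050 |
| 27/33 | 0.046 | 0.050 |
| 36/26 | 0.058 to 0.059 | about 0.050 |
| 26/36 | 0.043 | about 0.050 |

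The range at 36/26 is simulation spread. That split loses 10/72 = 14% overall, inside the planned 15%, but puts all of it in one arm (10/36 = 28%), so it is an extreme case.

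**3. Chance imbalance in neoplasm type.** The article gives no prevalences, so 20% to 50% is an assumption. For a category with K of 72 patients, the number in one arm is hypergeometric (36 drawn from 72), ignoring the small effect of blocking over time. A gap of 15 points means counts differing by at least 0.15 × 36 = 5.4, hence 6 when K is even; 20 points means 7.2, hence 8.

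| Prevalence (K) | P(gap ≥ 15 points) | P(gap ≥ 20 points) |
|---|---|---|
| 20% (14) | 13% | 3% |
| 33% (24) | 21% | 8% |
| 50% (36) | 24% | 10% |

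**4. What an imbalance or an adjustment could be worth.** Both depend on R², the share of AUC variance explained, which the article does not give. For assumed R² of 0.1 and 0.2:

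- A 15-point gap in a 50% category shifts the group difference by 0.15 × 2 × √R² = 0.09 and 0.13 SD, against a design effect of 0.75.
- Adjustment is worth 1/(1 − R²) = 1.11 and 1.25 times the sample, taking power at 30 per group from 81.5% to about 85% and 89%.

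At R² near zero, both vanish.

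**The case against.** The strongest reply is that very little turns on this. At 1:1 the two tests are practically the same and the sample size does not change. Unequal arms large enough to matter need one-sided dropout. The plan specifies intention-to-treat, with interpolation between valid scores and multiple imputation of a missing last day-5 score, so some patients with gaps stay in. This stands, and it limits the size of the point. It does not remove it: data collection stops for anyone who can no longer be managed per protocol, and the imputation rule names only those two patterns, so equal completers are not assured.

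It can also be said that equal variance is read into the text. That is fair, since the words are absent. The pooled-SD Cohen's d does not settle it either, because the effect size of 1.04 in the sample size section is also a pooled d, used beside an unequal-variance test. But the usual meaning of Student's t test is the pooled test, and the two sections need one name.

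On balance, the Discussion's main argument is wound pain and the midline-incision restriction. The balance remark is an addition and says only that types can be balanced. An unstratified single-centre trial with an unadjusted primary test is a legitimate design, and covariates are often left to an analysis plan. All of this stands. The absence of covariates is therefore not a defect in itself; the safeguard claimed for randomization is simply more than these blocks provide.

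**Conclusion.** The point holds at a modest level. The sample size and analysis sections name different tests for the primary endpoint, and the blocks described do not secure the balance of neoplasm type that the Discussion attributes to them.

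The size rests on the planning SDs of 2.9 and 3.6 carrying over to this trial and, for imbalance, on assumed prevalences of 20% to 50%. On those terms Student's type I error stays at about 0.050 with equal arms and ranges from about 0.043 to 0.059 at the extreme splits. The chance of a gap of 15 points or more in one category is about 13% to 24%.

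Four stronger inferences are tempting, and the article does not support them:

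- *The trial is underpowered or its primary test invalid.* The sample size reproduces under either test, and the level is affected only if completers are unequal.
- *Chance imbalance in neoplasm type would bias the result.* Under randomization the unadjusted test already allows for such imbalance in its type I error.
- *Neoplasm type is a known source of pain variance, so adjustment is worth a stated number of patients.* The text says only that types may create variability, then argues that they should matter little for wound pain. No association of type, or of age, with pain is given, so the gain is unknown and could be close to nil.
- *About one trial in four would show a 15-point gap.* The 24% is the 50%-prevalence case, the top of the range.

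**What to change.** 1. Name one primary test that is valid under unequal variances, in the same words in Sample size estimation and Statistical analyses. Two choices serve: the Welch t test, or a linear model of the AUC on arm and prespecified preoperative neoplasm type (ovarian, uterine, cervical) with heteroscedasticity-robust standard errors, giving the adjusted difference and 95% CI with the unadjusted Welch result alongside. Fix the choice before unblinding.
2. Reword the Discussion to say that randomization balances neoplasm type only in expectation, and leave the midline-incision restriction as the main argument.

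The cost is wording only. Recruitment was continuing when the article appeared, neoplasm type is part of the eligibility criteria, and no extra patients, visits or data are needed. Moving to Welch lowers power at 30 per group from 81.5% to 81.4%. The model uses two more degrees of freedom for a three-level factor and gains little if type is not prognostic; in that case plain Welch is sufficient.

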#### Subject recruitment

This randomized, sham-controlled, double-blind (subject- and assessor-blind) trial will be conducted in the Department of Obstetrics and Gynecology, at Queen Mary Hospital. Potentially eligible subjects who have scheduled for abdominal surgery for gynecological diseases will be invited to participate. Patients will be referred from a surgeon or gynecologist, and then a research assistant will approach the subjects at the pre-admission clinic or in the general ward pre operation. Patients will be screened and consented for the study. Following the consent, eligible participants will be block randomized into two groups: (I) acupuncture (*n* = 36) and (II) sham acupuncture (*n* = 36). All participants will undergo a standard operative procedure and receive postoperative analgesics according to usual practice. Treatment will be given within 2 h prior to the surgery, immediately after arrival on the ward, and daily following surgery for 5 days. Assessments will be conducted upon recovery, hourly at 6 h after surgery, then 4-hourly until day 2 and then 6-hourly until discharge. (See Fig. 1 for the study flowchart, and Fig. 2 for the assessment schedule).

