#### Postoperative acupuncture treatment (second to seventh acupuncture sessions) and acupoint justification

After the operation, the patient will be transferred to the ward after about 1 h. The subject will receive the second acupuncture treatment on the arrival to the ward. Afterwards, the subject will receive an acupuncture treatment every 24 h after the operation in the following 5 days (third to seventh acupuncture sessions). From the second acupuncture session onwards, a combined treatment approach of EA and AA using AA needles will be used.

The treatment procedure of EA, including needling procedure and electric-stimulation parameters, will be the same as the first acupuncture treatment described above, except that only four acupoints will be chosen from the additional acupoints list: GB26, GB34, GB41, HT3, HT7, KI4, KI6, LI11, LR5, LR14, LU7, PC6, SP6, SP14, SP15, SP16, SP21, ST23, ST25, ST27, ST34, CV4, CV12, and EX-CA1 with PC6 as the first choice. After completion of EA, AA will be performed as the first acupuncture treatment mentioned previously, but AA needles will be used. AA needles inserted will be retained and replaced every 3 days until discharge (in case of discharging before day 5) or day 5.

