### Measures

#### Outcome assessment

Subjects will be closely monitored during and after the operation. The primary outcome will be participants’ postoperative pain scores at rest measured by Numerical Rating Scale (NRS) for the first 5 days after operation. The secondary outcomes include postoperative NRS pain scores while coughing; dose and frequency of rescue analgesic use during hospital stay; time to recovery variables; QoR-9, SF-6D, and EQ-5D-5 L. If at any time point after the operation, a participant is unable to be managed according to the protocol for any reason, such as the development of complications, no further data will be collected. Telephone follow-up will be offered for participants discharged before day 5 (Fig. 2).

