### Primary outcome measure

#### Pain intensity by Numerical Rating Scale (NRS) at rest

The NRS for pain is a 0–10-point scale with 0 indicating no pain and 10 indicating worst possible pain. NRS pain scores will be measured at rest upon recovery, hourly at 6 h after surgery, then 4-hourly until day 2, 6-hourly until day 3 and then once daily until discharge. The NRS is a commonly used scale for clinical pain research. NRS is chosen because it is easier for patients to grade their pain intensity with numbers and it has been shown to correlate well with the Visual Analog Scale and Brief Pain Inventory as well as other pain measurements [36–39].

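### The 5-day pain AUC is undefined for patients whose scores stop on day 3 or earlier: NRS is scheduled to discharge, and the imputation rules do not cover a run of missing final scores

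*Protocol article*

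**What the plan says.** All references are to the protocol article.

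- **Outcome window.** Outcome assessment defines the primary outcome as "postoperative pain scores at rest measured by Numerical Rating Scale (NRS) for the first 5 days after operation". The objectives at the end of the Background also give the first 5 days, summarised as an AUC.
- **Schedule.** The primary outcome section takes NRS at rest "6-hourly until day 3 and then once daily until discharge". The coughing NRS ends at the same point. Subject recruitment gives a different schedule for the later days, "then 4-hourly until day 2 and then 6-hourly until discharge", which also ends at discharge.
- **Early discharge is foreseen.** The postoperative treatment section retains the auricular needles "until discharge (in case of discharging before day 5) or day 5". Outcome assessment adds: "Telephone follow-up will be offered for participants discharged before day 5", with a pointer to Fig. 2, which is not shown here.
- **Stopping of data collection.** Under Outcome assessment, if a participant cannot be managed according to the protocol for any reason, "such as the development of complications, no further data will be collected".
- **Analysis.** Statistical analyses specifies intention to treat, a trapezoidal AUC and Student's t test. It has two rules for missing NRS scores: linear interpolation when the gap lies between two valid scores, "or by multiple imputations if the missing score is the last pain score taken on day 5".
- **Expected loss.** Sample size estimation allows for 15% dropout.

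**The concern.** An AUC over a fixed window needs a value, observed or imputed, at both ends of the window. Here the schedule can end before the window does, and the imputation rule was written for a single missing final score, not for a run of them. For such a patient the analyst must choose between a shorter AUC, exclusion (which departs from intention to treat) and an improvised imputation. The article fixes none of these.

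The choice matters because a raw AUC falls as its window shortens. A stated objective is to learn whether acupuncture shortens recovery, including time to discharge. Window length could therefore differ by arm for reasons unrelated to pain. Patients whose data stop after a complication raise a second problem: their missingness is likely to be related to outcome.

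**Working it through.** **1. Which patients the two rules reach.** I take the primary outcome section's schedule as: recovery (0 h); hourly from 1 to 6 h; 4-hourly to 48 h; 6-hourly to 72 h; then 96 h and 120 h. That is 24 scores. (Hourly scoring over the first 6 h is my reading of an ambiguous phrase; it does not affect what follows.)

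| Last score obtained | Scores missing to 120 h | Covered as written | Not covered |
|---|---|---|---|
| Day 4 (96 h) | 1 | 1 (the day-5 score) | 0 |
| Day 3 (72 h) | 2 | 1 | 1 |
| Day 2 (48 h) | 6 | 1 | 5 |

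On this schedule a patient last scored on day 4 is covered. The gap begins with patients last scored on day 3 or earlier. Under the 6-hourly schedule in Subject recruitment, a patient last scored at 96 h would miss (120 − 96)/6 = 4 scores, 3 of them uncovered. The two schedules need reconciling in any case.

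**2. Whether a day-5 value closes the gap.** If a day-5 NRS is obtained by telephone, every earlier missing score lies between two valid scores and can be interpolated. If day 5 is multiply imputed instead, interpolating back from it works only if an imputed score counts as valid. Statistical analyses does not say that it does.

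**3. Who could be affected.** Patients discharged early who give no day-5 NRS, patients who withdraw, and patients whose data collection is stopped. The planned dropout alone is 0.15 × 72 = 10.8, about 11 patients. Inflating the sample for them protects power; it does not define their AUC.

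**4. The plan's own effect size.** Pooled SD = √((2.9² + 3.6²)/2) = √10.685 = 3.27. Then 3.4/3.27 = 1.04, as stated. At the design effect size, 0.75 × 3.27 = 2.45 AUC units. With 30 per group, power is 81.5%, and 30/0.85 = 35.3, so 36 per group and 72 in total. The sample size reproduces and is not in question. The units of the AUC are not given.

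**5. What truncation would do, if it were adopted.** This is illustrative. The pain profiles are assumptions: flat at NRS 2 or 3, linear from 5 to 1 or from 4 to 1, and exponential decline from 5.

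| AUC ends at | Lost, NRS-days | Share of 5-day AUC |
|---|---|---|
| Day 4 | 0.8–3.0 | 8–20% |
| Day 3 | 2.1–6.0 | 19–40% |
| Day 2 | 4.0–9.0 | 37–60% |

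Shift in the mean difference = (difference between arms in the proportion truncated) × (loss per patient). With assumed differences of 10 to 30 percentage points and losses of 2 to 6 NRS-days, this runs from 0.10 × 2 = 0.2 to 0.30 × 6 = 1.8 NRS-days. If the planning AUC is also in NRS-days, that is 0.2/2.45 = 8% to 1.8/2.45 = 73% of the design difference. If truncation is equal in both arms, the expected shift with no pain effect is zero. The width of this range shows that the documents do not determine the size.

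**The case against.** The strongest defence is that the plan already provides for early discharge. The telephone sentence stands in the paragraph that defines the 5-day outcome, its cut-off is the same day 5, and it points to the assessment schedule in Fig. 2. The natural reading is that the call completes the outcome, and the figure may say so. The day-5 imputation rule likewise presupposes a curve that ends on day 5, and the two rules can plausibly be chained.

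Much of this stands. A reader might infer that the plan prescribes an AUC cut off at discharge. It does not: no passage says so, and the 5-day definition and the intention-to-treat statement speak against it. A reader might also infer a seriously inflated type I error. Simulations can produce one. With no pain effect, 36 per arm and an assumed profile falling from 4.5 to about 1.4, truncation at 72 h gives 5–6% when 10% versus 5% are discharged by then, and 28–30% at 60% versus 30%. With one day-5 telephone score plus the stated interpolation, the rate stays at about 5% throughout. The discharge rates are assumed and the truncation is not in the plan, so these figures are not evidence of bias in this trial.

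Three things survive. The schedules still say discharge, and the telephone contact is offered without the text naming NRS. It cannot help patients who decline it, withdraw, or fall under the rule that stops data collection. And this is not detail left to an analysis plan: the article states a specific missing-data rule for its primary endpoint, and that rule does not fit the missingness its own schedule can create.

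**Conclusion.** The point holds as an incompletely specified primary endpoint. As written, the schedule and imputation rules do not guarantee a 5-day AUC for every randomised patient. On the primary outcome section's schedule, the undefined cases are patients last scored on day 3 or earlier who have no day-5 telephone score. The rule that stops data collection is the clearest source of missingness related to outcome.

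If those AUCs were truncated, and if acupuncture does bring discharge forward, the comparison would tilt towards acupuncture. Both conditions are hypothetical, and no size can be stated from the documents. The conclusion would narrow, but not disappear, if Fig. 2 schedules NRS by telephone to day 5: patients who withdraw or whose data collection stops would remain uncovered.

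**What to change.** 1. Statistical analyses: define the primary AUC on a fixed window of 0 to 5 days for every randomised participant.
2. Subject recruitment and both NRS sections: replace collection until discharge by collection until day 5, once daily by telephone after discharge, and give one common schedule that agrees with Fig. 2.
3. Outcome assessment: continue NRS collection to day 5 after departure from protocol management, unless consent is withdrawn. This concerns data collection only, not how the patient is treated.
4. Statistical analyses: extend multiple imputation from the single day-5 score to all trailing missing scores, and keep linear interpolation for interior gaps. The imputation model can be left to the analysis plan.

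The cost is wording plus one or two NRS questions in a telephone contact already offered. Trial status reports recruitment under way, so the collection changes should come first: scores not collected cannot be recovered later.
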